##### Outcomes

In line with CIHR knowledge translation guidance [54], 3 types of outcomes will be considered weekly (Table 2): (A) N&G and IAM use, (B) self-reported N&G information use, and (C) subsequent expected benefits.

##### Covariates

The main predictor will be participants’ SES as determined by the Quebec Index of Material and Social Deprivation, a validated ecological measure of the (education, income, and employment) disadvantage of a given geographic area (postal code) [121,122]. For each session, an index will be automatically assigned using (1) the reported postal code and the Canadian Deprivation Index Assignment Program (CDIAP) of the Public Health Agency of Canada when the data source is IAM and (2) the postal code matched to the session geotag via the “Dissemination Area Boundary File” of Statistics Canada and the CDIAP when the data source is Google Analytics. This will allow for the identification of low-SES participants (highest quintile of material and social deprivation). Using Google Analytics, participants’ demographic variables that will be considered in all analyses are age, gender, rural/urban location, and province. In addition, Web page–specific variables will be included to assess potential confounding and effect modifications. For each session, the type of device (Google Analytics: phone, tablet or laptop, and desktop), the audio-guide use (Google Analytics: yes or no), and the readability score of pages entirely read (automatic extraction and measurement using a text classifier validated for French) [123] will be collected.

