##### Measurement

N&G and McGill already use Google Analytics, an objective and reliable automatic data collection of N&G readers’ demographic characteristics and website use behavior (based on javascript codes in each Web page) [117-120]. IAM raters’ demographic data are collected with a questionnaire (linked to an anonymized identifier). The validated IAM questionnaire [53] collects self-reported information use and subsequent expected health/well-being benefits for parents and their child.

**Table 2 table2:** Types of outcomes monitored weekly.

Type	Outcome	Description and data source
A1	N&G^a^ sessions	Weekly number of unique sessions (Google Analytics)
A2	N&G read	Weekly proportion of sessions with at least 1 page entirely read (Google Analytics)
A3	IAM^b^ ratings	Weekly number of IAM questionnaires submitted
B1	N&G mediated	Weekly proportion of IAM ratings information used for the child of someone else
B2	N&G used	Weekly proportion of IAM ratings information used for oneself and one’s child
C	Expected benefits	Weekly proportion of IAM ratings expected health or well-being benefit for a parent and child, including at least 1 of the following self-perceived benefits (IAM choices of response): improvement of the health or well-being of a child, being less worried, prevention of a problem or the worsening of a problem, handling a problem, and being more confident to decide something with someone else

^a^N&G: *Naître et grandir*.

^b^IAM: Information Assessment Method.

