##### Study Size

On the basis of our 2-year pilot data (2014/09-2016/08), we anticipate about 5 million N&G sessions and 15,000 IAM ratings from Canadian participants during each period (pre- and postimplementation).

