### Timeline and Potential Challenges

Overall, 3 years will be needed to complete this project (Figure 3). Our phases are simple and well defined, and our planning is realistic. In phases 1 and 4, we anticipate no recruitment difficulties. Many parents have already agreed to be contacted for research, and N&G will facilitate the recruitment. Phase 2 is feasible, and the deliverables are realistic given that N&G has already implemented IAM, McGill and N&G have a strong OPR partnership, and N&G is committed to implementing IAM+N&G+. In phase 3, the large number of N&G readers guarantee a large sample. To control for potential seasonal variation in the number of sessions pre- and postimplementation, monitoring will be conducted during the same seasons. To control for contextual changes, variables such as type of device, age, gender, and location are covariates. We have opted for a prospective longitudinal study as monitoring is embedded in N&G routines. In addition, although randomization would provide a higher level of evidence, it was considered unethical to randomly assign low-SES parents to N&G+ or N&G information and impractical for such a popular website (contamination bias) [159]. Moreover, 3 typical potential sources of biases in longitudinal designs may not affect our study: the use of proportions will control for historical events, there will be no *respondent fatigue* as our 2-year pilot data showed that the monthly number of IAM raters is stable, and the social desirability bias will affect pre- and postimplementation periods in a similar manner.

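### Age, gender and location are to come from Google Analytics in every analysis, although B1, B2 and C are proportions of IAM ratings whose raters give their demographics by questionnaire, and no link between a rating and a session is described

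*Protocol article*

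**What the plan says.** All references are to the protocol article, Methods, Phase 3, unless stated.

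- **Covariates**, on demographics: "Using Google Analytics, participants’ demographic variables that will be considered in all analyses are age, gender, rural/urban location, and province". One source, every analysis.
- **Covariates**, on deprivation: the index is assigned by data source. IAM data use the postal code that the rater reports; Google Analytics data use the session's geotag.
- **Measurement**, on raters: "IAM raters’ demographic data are collected with a questionnaire (linked to an anonymized identifier").
- **Table 2** (Measurement): A1 and A2 come from Google Analytics, as "Weekly number of unique sessions (Google Analytics") and "Weekly proportion of sessions with at least 1 page entirely read (Google Analytics"). A3 is the "Weekly number of IAM questionnaires submitted". B1, B2 and C are proportions of ratings; B1, for example, is the "Weekly proportion of IAM ratings information used for the child of someone else".
- **Study Size**: "about 5 million N&G sessions and 15,000 IAM ratings from Canadian participants during each period".
- **Statistical Analysis**: potential confounders enter as fixed effects, and a quintile-by-period interaction gives the pre/post change in each quintile.
- **Discussion, Timeline and Potential Challenges**: "To control for contextual changes, variables such as type of device, age, gender, and location are covariates".

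**The concern.** There are two data streams with different populations: sessions of all readers, and ratings by the few who complete the questionnaire. The article separates the streams for the deprivation index but not for the demographics, where it assigns the reader stream to all outcomes. The rater's own answers, which the Measurement section says are collected, have no stated role as covariates.

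This matters because Phase 3 is an uncontrolled pre/post comparison; the Discussion explains why randomization was rejected and offers covariate adjustment as protection against contextual change. For B1, B2 and C the denominator is the set of ratings. If the age or gender mix of raters within a quintile differs between the periods, and expected benefit or use differs by age or gender, the quintile-specific change mixes that shift with any change in response among comparable raters. A covariate that describes all readers would hardly register the shift.

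**Working it through.** **1. Outcomes by source.** Table 2 gives two outcomes from Google Analytics (A1, A2) and four from IAM (A3, B1, B2, C). A3 is a count of ratings: rater mix is part of the outcome, and there is no rater-level response to adjust. The adjustment problem therefore concerns three outcomes, B1, B2 and C.

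**2. The plan's volumes.** Study Size gives about 5,000,000 sessions and 15,000 ratings per period. Linear scaling of other figures in the article to 9 months gives the same order:
- ratings: 34,021 in the 24-month pilot × 9/24 = 12,758
- sessions: 8.3 million visits from Canada in 2015 (Table 3) × 9/12 = 6.2 million

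Exact agreement cannot be expected, because the Canadian share of the pilot ratings is not given.

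**3. Ratings relative to sessions.** 15,000 / 5,000,000 = 0.0030, or 0.3%. At the low end, 12,758 / 6,225,000 = 0.0020, or 0.2%. This is ratings per session; the number of distinct raters is not stated.

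**4. What an unlinked covariate can detect.** Suppose that Analytics demographics enter the IAM models as averages over all sessions, and that each rating belongs to one session. With f = 0.003 and a gap of d points between raters and other readers on some characteristic, the all-session value misses the raters' value by (1 − f) × d:

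| d (assumed) | miss, (1 − f) × d | contribution of the gap to the all-session value, f × d |
|---|---|---|
| 10 points | 9.97 | 0.03 |
| 20 points | 19.94 | 0.06 |
| 40 points | 39.88 | 0.12 |

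In the same way, a 20-point shift in rater mix between periods moves the all-session value by 0.06 points. Even a complete change of rater category moves it by at most 0.3 points.

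**5. What would stay in the estimate.** With two rater categories, the shift in an outcome proportion due to mix alone is (change in share) × (difference in outcome between categories). The article gives neither factor for age or gender. Purely as an illustration, an assumed change in share of 0 to 20 points with an assumed difference of 11 points gives 0 to 0.20 × 11 = 2.2 points.

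**6. If a link exists.** If each rating carries the data of its own session, the mismatch in step 4 disappears. What remains is that the Setting section lets one session cover the person and a relative on the same IP address, so session data are still less direct than the rater's own answer.

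**The case against.** The strongest reply is that ratings may in fact be linked to sessions. Raters are site readers, the Covariates section speaks of assigning the deprivation index session by session even for IAM data, and the model has random effects for individual variables. With a link, the Analytics values would belong to the rater's session. This stands to the extent that the article neither states nor excludes a link. A reader might infer that the IAM outcomes are adjusted for the wrong people; the document does not support that, because it requires that no link exists.

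Three further points stand. First, the shift that IAM+ is meant to bring, more low-SES parents, is already in the model through the reported postal code and the quintile-by-period interaction; only mix within a quintile is at issue. Second, a change in rater age or gender may follow from IAM+ itself, so adjusting for it answers a different question from not adjusting. Third, for A3 reader mix is a relevant covariate, since it describes who could have rated.

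It can also be said that a condensed article leaves the mapping of covariates to outcomes to a fuller document. That would answer silence. Here the article names a source and applies it to all analyses, directly after splitting the deprivation index by source.

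**Conclusion.** The point holds as a conflict between the Covariates and Measurement sections over where raters' demographics come from, with consequences for B1, B2 and C. Unless ratings are linked to sessions, the stated covariates describe a reader population in which ratings amount to 0.2% to 0.3% of sessions, and they cannot deliver the control for rater mix within a quintile that the Discussion expects of them. With a link, the rater's own answers are still the more direct measure.

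Two stronger readings should be resisted. The 2.2 points in step 5 are not an estimate of bias: both factors are assumed and either could be zero. And 0.3% is not the share of readers who rate, because one person may contribute several ratings or sessions. The main predictor is sound on this point, since the quintile for IAM data uses the rater's reported postal code. The matter is worth correcting before the analysis, but it does not invalidate Phase 3.

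**What to change.** Rewrite the demographic sentence in Covariates by data source, as is already done for the deprivation index:

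- **A1, A2:** age, gender, rural/urban location and province from Google Analytics.
- **B1, B2, C:** the rater's questionnaire demographics, to the extent that the questionnaire collects these items, with rural/urban location and province from the reported postal code.
- **A3:** keep reader-mix covariates, or report the counts by rater strata.
- **Device type:** use it for the IAM outcomes only if a rating-to-session link exists and is described.

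Align the statement on contextual changes in Timeline and Potential Challenges. For B1, B2 and C, report the unadjusted estimate beside the adjusted one, because a change in rater mix may be an effect of IAM+.

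The cost is mainly wording, since raters' demographics are already collected. Two things need checking: the article does not list the questionnaire's demographic items, so the presence of age and gender must be confirmed, and so must the tie between the anonymized identifier and each rating. The small downside is that covariate sets differ between outcomes.

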##### Study Size

On the basis of our 2-year pilot data (2014/09-2016/08), we anticipate about 5 million N&G sessions and 15,000 IAM ratings from Canadian participants during each period (pre- and postimplementation).

##### Anticipated Results

The IAM+N&G+ will result in an increase of all outcomes (N&G and IAM use, self-reported N&G information use, and subsequent expected health and well-being benefits for parents and children such as *decreased worries* and *health improvement*, respectively).

##### Statistical Analysis

Linear mixed modeling will integrate spatial analytics (geomatics) and account for the clustered nature of the data. The pre/post status, the SES quintile of deprivation, and potentially confounding variables will be included as fixed-effects covariates. The inference model will incorporate random effect terms for individual variables and Web page–specific variables. For each outcome, an interaction term of the SES quintile of deprivation and the pre/post status will be included to assess the pre/post change for each quintile. Estimated regression coefficients and variance parameters will be reported along with appropriate confidence intervals.

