N&G partnered with investigators from McGill University to validate and implement the IAM to continuously assess and improve content shared on the N&G website and newsletter [49-53]. In line with the Canadian Institutes of Health Research (CIHR)’s definitions [54], the IAM is a knowledge translation tool for monitoring N&G information use, and its impact on parents is measured by expected health/well-being benefits. It is also fostering parent engagement by enabling parents to interact with N&G editors by providing feedback on the information content. The IAM questionnaire includes 7 questions (with clickable answers and 2 comment boxes), allowing users to rate on the situational relevance, cognitive/affective impact, intention to use and expected benefits of specific information content (N&G information page), and write comments.

During our pilot phase (September 1, 2014, to August 31, 2016), we collected 34,021 IAM ratings (completed IAM questionnaires) from parents, relatives, and professionals (education, health, and social services) who read N&G content. In line with studies on social inequalities in Web information use [55-61], the statistical analysis of these ratings revealed a social gradient: low-SES parents underuse N&G and the IAM (Figure 1). Results also indicated that low-SES parents are more likely to report decreased worries and increased confidence as a result of using N&G information [50]. There is a need to understand this gradient to improve N&G content and reach low-SES parents and a need to explore how the use of knowledge translates into health and well-being outcomes for low-SES parents and children.

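### For the weekly counts A1 and A3, the linear model puts the SES-by-period interaction on an additive scale, so equal percentage gains give a negative low-SES interaction while the low-SES share is unchanged

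*Protocol article*

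**What the plan says.** Under Phase 3, Statistical Analysis, the article names one model family for all outcomes: "Linear mixed modeling will integrate spatial analytics (geomatics) and account for the clustered nature of the data". The abstract repeats it. The same section continues: "For each outcome, an interaction term of the SES quintile of deprivation and the pre/post status will be included". The stated purpose of the term is to estimate the before/after change in each quintile.

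Table 2 lists six weekly outcomes. A1 is the number of sessions and A3 is the "Weekly number of IAM questionnaires submitted"; both are counts. A2, B1, B2 and C are proportions. No link function, offset, rate or transformation is mentioned for any of them.

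The Rationale reports from the pilot that "low-SES parents underuse N&G and the IAM". Objective 3 asks whether the new versions lead to a higher proportion of low-SES parents engaging. The section on timeline and potential challenges argues that working with proportions deals with historical events.

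**The concern.** An untransformed linear model for a count measures the interaction as a difference of absolute changes. When quintiles start from different levels, the same percentage change produces different absolute changes, so the interaction takes its sign from the baseline gradient. Objective 3 is a question about proportion, and the additive contrast does not answer it for A1 and A3.

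The design makes this matter more. It is a before/after comparison without a concurrent control, so the contrast between quintiles is the main protection against general changes in traffic. On the additive scale, a traffic trend that is proportional in all quintiles passes straight into that contrast. The article's defence based on proportions does not reach A1 and A3, which are not proportions.

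**Working it through.** **The plan's own volumes.** Study Size anticipates about 15,000 ratings and 5 million sessions in each 9-month period. Prorating the pilot gives 34,021 × 9/24 = 12,758 ratings. Prorating the 2015 Canadian visits in Table 3 gives 8.3 million × 9/12 = 6.2 million sessions. Neither reproduces the stated figure closely, but both stated figures are approximate and the point does not depend on them. The stated figures are used below.

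**Weekly totals** (39 weeks): 15,000/39 = 385 ratings; 5,000,000/39 = 128,205 sessions. The average per quintile is about 77 ratings and 25,600 sessions a week.

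**Formula.** Let Q1 be the least and Q5 the most deprived quintile, with baseline weekly means μ1 and μ5, and let every quintile gain the same fraction g.
- Additive interaction = gμ5 − gμ1 = g(μ5 − μ1). It is negative whenever μ5 < μ1.
- Log-scale interaction = log(1+g) − log(1+g) = 0, a ratio of rate ratios of 1.
- Q5 share = μ5(1+g)/[Σμ(1+g)] = μ5/Σμ, unchanged.

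The result is the same whether g comes from the intervention, from a trend, or from both.

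**Assumed example.** Q5/Q1 = 0.7 with equal steps between quintiles gives weights 1, 0.925, 0.85, 0.775 and 0.7, which sum to 4.25; g = 0.20.
- A3: μ1 = 384.6/4.25 = 90.5 and μ5 = 63.3. Interaction = 0.20 × (63.3 − 90.5) = −5.4 ratings a week.
- A1: μ1 = 128,205/4.25 = 30,166 and μ5 = 21,116. Interaction = 0.20 × (21,116 − 30,166) = −1,810 sessions a week.
- Q5 share: 0.7/4.25 = 16.5% before and after.

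**Sensitivity to the assumptions.** The simulation had 1,000 runs per scenario, 39 independent weeks per period and a two-sided 5% level. It tested the Q5-versus-Q1 difference in before/after change of weekly means, with +20% in every quintile:

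| Q5/Q1 | A3 interaction per week | A3 flagged: Poisson / variance 3 × mean | A1 interaction per week | A1 flagged: Poisson / variance 500 × mean |
|---|---|---|---|---|
| 0.9 | −1.6 | 9% / 6% | −540 | 100% / 8% |
| 0.7 | −5.4 | 47% / 19% | −1,810 | 100% / 32% |
| 0.5 | −10.3 | 93% / 52% | −3,419 | 100% / 81% |

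The log-ratio contrast was flagged in 4% to 7% of runs in every scenario examined. This is a simplified comparison of means, not a fit of the full mixed model.

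**Proportions.** With 77 ratings in a quintile-week, the binomial standard error is √(0.654 × 0.346/77) = 0.054 for C (65.4% in the pilot) and √(0.181 × 0.819/77) = 0.044 for B1 (18.1%). If the most deprived quintile supplied only 10% of ratings (an assumption; about 38 a week), these become 0.077 and 0.062. A2 rests on about 25,600 sessions per quintile-week. Precision varies from week to week for B1, B2 and C, but this does not show that the linear intervals fail.

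**The case against.** The article does not say that a negative interaction will be read as failure. The term is there to estimate each quintile's own change, and in the example the most deprived quintile's change is positive on either scale. A reader might infer that equal gains will be reported as a widening social gap; no section says so. The absolute gap in sessions does widen in the example, from 9,050 to 10,860 a week, so an additive statement would be true on its own scale. All of this stands. What remains is that this scale does not match Objective 3. If that objective is read instead as the fraction of low-SES parents who engage, a uniform gain is an improvement, and a negative interaction is no measure of that either.

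A reader might also extend the point to all six outcomes and conclude that the intervals for the proportions are wrong. The documents do not support this. The denominators are adequate on the stated volumes, A2's is very large, and equal variance is not stated. For C the direction could reverse, because the Rationale reports that low-SES parents more often mention two of the benefits. If they started at an assumed 70% against 60%, a common factor of 1.1 gives +7 against +6 points, an interaction of +1 point in their favour.

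The size is open. Figure 1 shows ratings relative to subscribers by centile of material deprivation, not counts by quintile, so the baseline ratio for A1 or A3 cannot be taken from it.

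Finally, a condensed article may leave links and transformations to a fuller plan, and the session-level covariates and page-level random effects may point to a finer unit of analysis. But the model family is stated here, twice, and A1 and A3 are defined only as weekly numbers.

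**Conclusion.** The point holds for A1 and A3. Given lower baseline use in low-SES quintiles, an untransformed linear interaction is negative under equal relative gains or a common proportional trend, while the low-SES share stays constant. The direction follows from the article's own pilot finding, provided that underuse shows as lower weekly counts in the most deprived quintile.

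The magnitude depends on a gradient, a gain and an overdispersion that the article does not give. At +20% it runs from about −2 to −10 ratings and from −540 to −3,419 sessions a week over the baseline ratios tried. The chance of a significant result runs from close to the nominal level to near certainty. For the four proportions, a different model would be a refinement and does not correct a demonstrated error.

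**What to change.** For A1 and A3, replace the linear model with a count mixed model that allows overdispersion, for example negative binomial with a log link. Report the quintile-by-period interaction as a ratio of rate ratios with its interval. Alternatively, model the low-SES share of weekly sessions and of weekly ratings directly, which is closest to Objective 3. Either choice removes from the interaction a proportional trend common to all quintiles. Neither removes such a trend from the overall before/after change.

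Subscriber numbers should not serve as the offset, because subscriptions may themselves respond to the new version. A population offset that is stable over time cancels from the interaction and is not needed for it.

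As a secondary refinement, analyse A2, B1, B2 and C with a binomial (logit) mixed model on weekly events and denominators, so that weeks are weighted by their denominators, and report back-transformed percentages.

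The cost is a change in the analysis wording and somewhat heavier fitting, with no new data collection. The downside is that ratio effects must be back-transformed into sessions and ratings for the Web editors.
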